
suggests that a reduction in 10 mg/dl in LDL potentially reduces CVD events by 5%. We present results from a two-step approach to the power calculation intended to detect differences of 10 mg/dl or greater between the control and each intervention arm, as well as a 5 to 10 mg/dl difference between the most and least effective intervention arms. Thus Step 1 compares each of the intervention arms versus control (3 comparisons); Step 2 compares each of the intervention arms to each other arm (3 additional comparisons). For these sample size estimates, we assumed a standard deviation of 28 mg/dl (based on a prior RCT). The nominal experiment-wise two-sided Type 1 error rate of 0.05 was maintained in step 1, by using a Bonferroni correction (i.e.,  $\alpha=0.017$ , derived as  $0.05/3$  for 3 comparisons) and in Step 2 by using Tukeys honest significant difference. Many possibilities exist for differences between the three interventions and control; the table below considers three possibilities for a sample size of 160 per group. For differences of 10 mg/dl or larger between intervention and control, simulation studies indicate at least 80% power to detect differences between all 3 interventions and control. For differences of at least 10 mg/dl between interventions, we have at least 90% power to detect at least one difference among arms; for differences of 5 mg/dl or larger we have 82% power to detect at least one difference among arms. To ensure our sample size of 160 for the 12 month endpoint, we assumed a dropout rate of 14.5 % and inflated the sample size to 187 in each arm ( $n=748$  in the entire study) . Sensitivity Analyses: Between November 2015 and July 2016 the device failed at rates that exceeded rates obtained in our earlier studies. We anticipated that this might increase the variance of the primary outcome, with some subjects perhaps responding positively with increased compliance to statin medication and some negatively with decreased compliance. Positive responses might reflect increased intervention from study staff, or the swapping out of one device for another spurring increased compliance. Negative responses might reflect frustration, particularly on the Process arm or the Process & Outcome arm, with the inconsistent devices. We note that our completion rates for lab visits are close to our expected rates of 85%, suggesting that the device issue has not had an impact on subject retention. APPROACH 1: As a sensitivity analysis, we increased our assumed variance by 7% (SD 29 versus SD of 28) and we decreased our effect size in the Process alone and the Process & Outcome arms by 10%. Given that only XX subjects were affected for over a month, we believe this to be a very conservative calculation of the negative impact of the device issue. Table 2 above shows that, while our power has declined somewhat, we still have close to 80% power or APPROACH 2: As a sensitivity analysis, we increased our assumed variance by 15% (SD 30 versus SD of 28). Given that only XX subjects were affected for over a month, we believe this to be a reasonable assumption. Our study was designed to detect differences of 10 mg/dl between control and treated group as this difference is deemed clinically relevant. Table 3 below shows there is some decline in power, but overall we retain good power to complete the study successfully under a number of scenarios.

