2. For each subject we will create a variable quantifying the proportion of their treatment time in the window with properly functioning devices. For most subjects, this variable will be 1, but for a subjects with say 2 months in the window of faulty devices, this would be  $61/356=.83$ . We will additionally include a variable indicating whether a subject required a device swap. These variables will be included in the primary regression model. Of interest is whether the LDL levels at 12 months (change from baseline) are associated with either variable, and whether the association between LDL level at 12 months and treatment group is confounded by either variable. Additionally, we anticipate that any effect of device malfunction should primary affect the response of subjects on the Process or the Process & Outcome arms. We will thus repeat our analyses separately with these two arms.
3. We will use a logistic regression to determine whether the likelihood of completing the study (lab visit at 12 months) is associated with the proportion of time with a properly functioning device, or the occurrence of a device swap.
4. We will explore patterns of adherence over time as a function of device type. Unfortunately having a faulty device means that we do not have reliable adherence data during the period of device failure. Thus questions will be explored using regression models with data from the periods when the devices were functioning normally. These include:
  - a. Do mean rates of compliance differ by device for subjects randomized to a single device for the entire study period. Does the decline over time in compliance differ by device for subjects randomized to a single device over the study period.
  - b. On average, during the period when our devices returned to normal functioning, are compliance rates similar for subjects who were exposed to faulty devices versus subjects who had normally functioning devices. These will be GEE models with a binary outcome for each day (compliant or not). The predictors include time on study, an indicator variable of whether the subject was on study during the period when the devices failed (or a quantitative variable indicating proportion of time with a functioning device), and an indicator variable for whether subjects experienced more than one device. The analysis will be carried out for the study as a whole (including a treatment indicator), and for each treatment group.

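### At the 10 mg/dl design difference, Approach 1's own inputs leave each sweepstakes arm with about 64% power against control (Bonferroni) or 73% (Holm), not close to 80%

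*Combined protocol and SAP*

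**What the plan says.** The power text is in the protocol under Accrual (Power and Sample Size, then Sensitivity Analyses).

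- **Design case.** SD 28 mg/dl, two-sided testing, three comparisons with control: "The nominal experiment-wise two-sided Type 1 error rate of 0.05 was maintained in step 1, by using a Bonferroni correction", that is, 0.05/3, given as 0.017. On sample size, "the table below considers three possibilities for a sample size of 160 per group". Stated power against control is at least 80% for differences of 10 mg/dl or more. On the target: "Our study was designed to detect differences of 10 mg/dl between control and treated group".
- **Approach 1.** "we increased our assumed variance by 7% (SD 29 versus SD of 28) and we decreased our effect size in the Process alone", and the same 10% cut applies to Process & Outcome. The conclusion, citing Table 2, is that "while our power has declined somewhat, we still have close to 80% power". The sentence then breaks off.
- **Approach 2.** SD 30, with no effect reduction in its visible description. The conclusion, citing Table 3, is that "overall we retain good power to complete the study successfully under a number of scenarios".
- **Where the failures should act.** The Analysis Plan (Sensitivity Analyses, Device Failure, item 2) expects that "any effect of device malfunction should primary affect the response of subjects on the Process or the Process & Outcome arms".
- **Multiplicity in the SAP.** Section 2.1 tests each arm against control with Holm-Bonferroni, not plain Bonferroni.

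**The concern.** The design case starts at about 80% power per comparison, with nothing in reserve. Approach 1 then lowers the effect and raises the SD together in two of the three incentive arms. A result still close to 80% in those arms is not what one would expect.

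Those two arms carry the process incentive (Specific Aims 1 and 3). If the report relies on a power near 80%, a non-significant sweepstakes-arm result could be given more weight as evidence of no effect than it can bear. The device-failure analyses cannot correct that impression, because both the protocol and the SAP call them exploratory and not powered for testing.

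**Working it through.** **Inputs** (all from Accrual unless noted): n = 160 evaluable per arm; two-sided level 0.05/3 = 0.0167; SD 28 (design), 29 (Approach 1), 30 (Approach 2); design difference 10 mg/dl; 10% cut in the sweepstakes arms, so 0.9 × 10 = 9 mg/dl; Holm from SAP section 2.1. Completion is reported as close to the expected 85%, and 0.85 × 187 = 159, so 160 still applies. The stated variance increases are consistent with the SDs: 29²/28² = 1.073 and 30²/28² = 1.148.

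**Formula.** For one comparison with control, SE = SD × √(2/160) and non-centrality = difference / SE. Power comes from the non-central t with 318 df and critical value 2.407.

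**Step 1: the plan's own figure.** SE = 28 × 0.1118 = 3.130; 10/3.130 = 3.194; power 78.4% (78.8% by normal approximation). The stated 80% is roughly reproduced per comparison. It is not reproduced as power for all three at 10 mg/dl, which is 59% (Bonferroni) or 75% (Holm).

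**Step 2: the same formula with the sensitivity inputs, Bonferroni level.**

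| Case | SD | Difference | SE | Non-centrality | Power |
|---|---|---|---|---|---|
| Approach 1, Process or Process & Outcome | 29 | 9 | 3.242 | 2.776 | 64.4% |
| Approach 1, Outcome | 29 | 10 | 3.242 | 3.084 | 75.1% |
| Approach 2, any arm | 30 | 10 | 3.354 | 2.981 | 71.7% |
| SD 30 with the 10% cut (not in the plan) | 30 | 9 | 3.354 | 2.683 | 60.9% |

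The normal approximation for the first row is Φ(2.776 − 2.394) = 64.9%. For 80% power in that row, n = 2 × (29/9)² × (2.394 + 0.842)², or 218 evaluable per arm. Alternatively, with 160 per arm, the difference before the cut would have to be 3.242 × 3.236 / 0.9 = 11.7 mg/dl.

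**Step 3: Holm and joint power.** Simulation of 300,000 four-arm trials with a shared control and pooled variance; effects in the order Process, Outcome, Process & Outcome.

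| Effects, SD | Sweepstakes arm, Holm | Outcome arm, Holm | All three, Bonferroni / Holm |
|---|---|---|---|
| 9, 10, 9; SD 29 | 73% | 81% | 44% / 62% |
| 10, 10, 10; SD 30 | 79% | 79% | 50% / 67% |
| 9, 10, 9; SD 30 (not in the plan) | 70% | 77% | 40% / 57% |

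In the first row, power for at least one significant arm is 89%.

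**Step 4: larger effects.** Take undiluted effects of 10, 15 and 20 mg/dl in any arm order, apply the 10% cut to the two sweepstakes arms, and use SD 29. All-three power is 64% to 74% with Bonferroni and 79% to 86% with Holm.

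**The case against.** The strongest reply is that the quoted sentence describes a table that cannot be seen and is cut off mid-phrase. Effects of 10, 15 and 20 are a plausible scenario for it, because before the failures they reproduce the protocol's 82% power for at least one difference among the incentive arms. Under Approach 1 that pattern gives 79% to 86% for all three comparisons with Holm. This stands: a reader might infer that Table 2 is wrong, and the documents do not support that.

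Three other strong readings also go too far.

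- **That the claim fails on every definition of power.** It does not. Power for at least one arm is 89% even at 9, 10 and 9 mg/dl, and dropping the multiplicity correction gives 79% for a sweepstakes arm. Neither, however, is power for a given arm at the stated level.
- **That the re-powering was the reason for carrying on unchanged.** The protocol only says that good power is retained.
- **That Approach 2 had to include the effect cut.** The two approaches are alternative scenarios, and combining them is a reviewer's choice.

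Two technical points remain. The SAP's Holm procedure is more favourable than Bonferroni, so 64% alone would understate power under the planned test. Adjustment for baseline LDL could also help if the stated SD is unadjusted. Assuming a baseline-to-change correlation of 0.3 to 0.5, Bonferroni power for a sweepstakes arm would be 69% to 79%. The documents give no correlation and do not say whether the SD is already adjusted.

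Finally, the protocol presents Approach 1 as a deliberately pessimistic case, and enrollment is closed. New power figures therefore change neither the sample size nor the analysis.

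**Conclusion.** The point holds in a limited form. At the protocol's 10 mg/dl design difference, Approach 1 gives each sweepstakes arm about 64% power against control under the stated Bonferroni level and about 73% under the SAP's Holm procedure. The fall from the reproduced design figure of 78% (Bonferroni) is 14 percentage points. The chance of missing the reduced 9 mg/dl effect is about 36% (Bonferroni) or 27% (Holm). Outcome versus control, at 75% or 81%, is near the claim.

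This rests on 160 evaluable per arm, the SDs as stated with no further gain from covariates, and, for Holm and joint power, true effects of 9, 10 and 9 mg/dl. It does not show that any entry in Table 2 or Table 3 is wrong. Approach 2 as defined gives 72% (Bonferroni) or 79% (Holm) per comparison, so its conclusion is defensible under Holm but should be stated as a number.

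**What to change.** 1. Replace the Approach 1 sentence with per-arm power at 10 mg/dl under the multiplicity procedure that will be used: 64% (each sweepstakes arm) and 75% (Outcome) with Bonferroni, or 73% and 81% with Holm. Name the same procedure in the protocol and the SAP.
2. Label any figure near 80% with the effect pattern and the definition of power it assumes (one comparison, all three, or at least one).
3. For Approach 2, replace the general statement of good power with 72% per comparison (Bonferroni) or 79% (Holm). A row combining SD 30 with the 10% cut (61% or 70% for a sweepstakes arm) is optional.
4. State that a non-significant sweepstakes-arm result will be reported with its confidence interval set against 10 mg/dl, and not as evidence of no effect.

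The cost is a short recalculation and a few sentences. No participants, visits or analyses are added; the stated power simply becomes less favourable.

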
#### **Key inclusion criteria**

Individuals at high risk of a cardiac event, specifically one of the following: Individuals with clinical ASCVD (defined as diagnosis with myocardial infarction, stroke, or peripheral vascular disease) with an LDL greater than or equal to 100 mg/dl ; Individuals with Diabetes (between the ages of 40-75) with an LDL greater than or equal to 100 mg/dl; Individuals without clinical ASCVD or diabetes with LDLC with an LDL greater than or equal to 100 mg/dl and estimated 10-year ASCVD risk 7.5%; Individuals without clinical ASCVD or diabetes with LDL cholesterol 190 mg/dl A prescription filled for a statin medication within the last 12 months (derived from pharmacy records or EHR); Imperfect statin adherence level as defined by one of the following: Medication Possession Ratio (MPR) less than or equal to 80% A score 0 on the 8-item Morisky Medication Adherence Questionnaire completed during enrollment

#### **Key exclusion criteria**

Patients will be excluded if they 1) are under 18 years old; 2) have a contraindication to further statin use or have suffered statin side effects, such as myopathy; 3) will not or cannot give consent; 4) have a history of active or progressive liver disease or 5) are participating in another clinical trial with related aims, 6) have co-morbidities likely to lead to death within a short period (e.g. metastatic cancer), or 7) are prescribed by their doctor PCSK9 inhibitor injections coupled with statin therapy.

## **Vulnerable Populations**

**Children Form**

**Pregnant women (if the study procedures may affect the condition of the pregnant woman or fetus) Form**

**Fetuses and/or Neonates Form**

**Prisoners Form**

**Other**

☒ **None of the above populations are included in the research study**

**The following documents are currently attached to this item:**

*There are no documents attached for this item.*

### **Populations vulnerable to undue influence or coercion**

All participants will be mentally able, literate, working adults participating in the study of their own free will. This population is not unusually vulnerable.

### **Subject recruitment**

Study participants will be recruited by Penn Medicine/LGH or CVS Caremark on behalf of the health plans as a business associate in its role as a PBM. Potential CVS participants will be identified by reviewing CVS Caremark pharmacy claims records using our eligibility criteria of statin use and MPR less than 80%. All potentially eligible employees within the CVS-covered group will be contacted via existing communication channels through CVS. Potentially eligible employees will have evidence of diabetes medication use and/or CVD medication use in the CVS pharmacy database. These individuals will be sent letters (paper or email) describing the study and inviting them to enroll. Participants will also be recruited from the University of Pennsylvania Health System/LGH. Potential participants will be identified by monitoring laboratory data, via weekly queries of the EPIC electronic medical record database. Primary care providers in the Penn Health System/LGH will be notified when one of their patients are eligible to participate via the secure UPHS email system. Providers will have one week to opt patients out of receiving the recruitment letter if they feel the patient is not fit to participate in research. All eligible Penn Health System/LGH patients will be mailed letters by the study staff inviting them to sign up on the study website. Follow-up phone calls and emails will also be completed with these patients since contact information will be available through EPIC. If a participant has a calculated LDL value meeting study inclusion criteria within the past 4 weeks, that value will be used as their baseline LDL and they will not need to complete the baseline lab test. Interested participants will sign up online or by phone with a study coordinator based at UPENN and will be asked to provide informed consent. These individuals will have the option of entering data related to eligibility and their demographic and clinical characteristics through the Way to Health internet portal or by phone. Each potential participant will visit a local participating laboratory (through the Quest national chain of commercial laboratories or their doctor if they are from Penn Medicine/LGH) to confirm that their LDL is 100 mg/dl. The Quest corporation has 24 hour appointment scheduling and 2,000 lab locations; these locations are in every state as well as Puerto Rico. The enrollment interview and baseline labs will allow investigators to determine final eligibility for the study. Our group has agreements in place with the Quest chain allowing research participants nationwide to have phlebotomy (blood draws). In the context of generous participation incentives (as will be provided in this study), the requirement of providing biological specimens at local laboratories has not been a barrier to program implementation. In another ongoing study, we have used Quest to enable 500 participants to get labs drawn at local laboratories. Randomization will be performed through the Way to Health platform. Randomization will be stratified by employer (should more than one employer be involved to recruit a sufficient number of participants) and will use block randomization with variable block sizes. After reviewing the intake data and LDL, research staff will notify each participant of assignment using their preferred means of communication. All participants will receive an electronic pill container through the mail and will receive careful instructions about study procedures for their assigned arm. Throughout the study, coordinators will remain available to answer questions about device use and other study procedures.

Will the recruitment plan propose to use any Penn media services (communications, marketing, etc.) for outreach via social media avenues (examples include: Facebook, Twitter, blogging, texting, etc.) or does the study team plan to directly use social media to recruit for the research?

No

**The following documents are currently attached to this item:**

*There are no documents attached for this item.*

**Subject compensation\***

Will subjects be financially compensated for their participation?

Yes

**The following documents are currently attached to this item:**

*There are no documents attached for this item.*

**If there is subject compensation, provide the schedule for compensation per study visit or session and total amount for entire participation, either as text or separate document**

Participants will receive study instructions after they are randomized that detail the administration of additional incentives. Administration of Process Incentives for Daily Adherence. The process financial incentive involves a daily sweepstakes for taking the statin medication. The sweepstakes has two components a high probability/low value reward as well as a low probability/high value reward. We will assign each participant in the Process (arm 1) and Process plus Outcome (arm 3) a two-digit number. Each day, the pill container will automatically upload the previous days data about each participants statin adherence via a wireless internet connection to the Way to Health database at UPENN. We will let each participant pick a two-digit sweepstakes number. Each day, Way to Health software will compare this number with a random two-digit number generated by Way to Health to determine eligibility for sweepstakes awards. For a participant who was adherent the previous day, if the two digit number matches exactly (probability of 1 in 100), the participant will win \$50. When the two-digit number does not match, but either the first digit or second digit matches, the subject will win \$5 (probability of 18 in 100). The expected value of this sweepstakes is \$1.40/day such that total winnings over the 12-month trial for a participant with perfect adherence will have an average expected value of \$511. An important feature of the sweepstakes is that each eligible participant will receive daily messages about the amount they won. Non-adherent participants will also receive daily feedback about whether they would have won if they had been adherent. This program incorporates key aspects of optimal design, including objective and reliable confirmation of behavior change at frequent intervals, large potential payments to reinforce the target behavior, frequent reinforcement using high probability/low value awards, and the use of anticipated regret, a powerful motivator. We set the expected value of the sweepstakes at \$1.40/day based on our previous success in significantly affecting weight loss and medication adherence with this design. In addition, there is evidence that a patient with established CVD has health expenditures ranging from \$4,500 to as high as \$30,000 per year, suggesting that \$1.40/day incentives if effective, could be cost-effective due to the potential savings in avoiding future CVD events. Administration of Outcome Incentives for LDL. Participants in the outcomes arms (arms #2 and #3) will receive payments if their LDL decreases at least 10 mg/dl in the 3 months since the last visit. Over a year, these payments will be equivalent in magnitude to those in the process arm. The 3-month payment for the Outcome arm (arm #2) will be \$126, while the payment for the Process with Outcomes Incentive arm (arm #3) will be half this value, or \$63. Notably, if a participant in the Outcomes arm or the Process plus Outcomes arm achieves a reduction in LDL 20 mg/dl during one quarter of the trial and that reduction persists during the next quarter, the participant would be eligible for the outcome incentive at the end of both quarters, even if no further reduction in LDL took place during the second quarter. For instance, if a patient in the Outcome arm had an LDL decrease from 150 to 130 mg/dl between baseline and month 3, and also had an LDL of 130 mg/dl at month 6, that person would receive the incentive payment at month 3 and month 6. Participants in the intervention arms will be informed if they fail to meet adherence or LDL goals, and thereby are not eligible for payments. Providing this feedback may also improve adherence by taking advantage of anticipated regret. Additionally, patients will receive \$50 after enrollment, initial blood work, and setting up the Glow Caps. A subset of participants will receive \$100 after enrollment to test whether higher participation incentives increase recruitment rate. Participants will receive \$50 for each subsequent lab check and \$75 for the 12 month LDL check, for a total of \$325 if

all lab tests are completed.

